### Determination of Sample Size

The primary outcome of the trial is to assess whether the CAD system can reduce in-hospital mortality. On the basis of data from the NTUH institutional database [19], the ICU mortality rate in 2023 to 2024 is estimated at 28%. A projected reduction to 25% was used for the sample size calculation. With an intraclass correlation coefficient of 0.01, a power of 80%, and a 1-sided α of 5%, each group requires 5450 patients, resulting in a total sample size of 10,900. This design is expected to provide sufficient power to detect clinically significant improvements in patient outcomes (Figure 3).

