## Methods

### Research Design

This study adopts a 2-phase design, beginning with a pilot study followed by a multicenter cluster randomized clinical trial. The pilot phase focuses on integrating a CXR CAD system into the hospital’s medical information systems, ensuring smooth functionality within the clinical workflow. The system will undergo testing and initial evaluations in the emergency intensive care and ICU at NTUH over a period of 6 to 12 months.

Building on the pilot phase, the multicenter clinical trial involves ICUs from NTUH, FJCUH, and MSGH. A total of 18 ICU units will participate, with NTUH contributing 14 units and the remaining hospitals contributing 2 units each. These units will be randomized into AI-assisted and control groups. Stratification is based on ventilator use, with randomization conducted within each stratum using uniform distribution. The AI-assisted group allows physicians to access real-time predictions from the CAD system during patient care. These predictions, generated within seconds, focus on identifying critical conditions, such as NGT misplacement, ETT misplacement, and pneumothorax. However, physicians in the control group will adhere to standard procedures without viewing AI-generated predictions, though the CAD system will still analyze images for internal validation. To minimize potential bias, both the outcome assessors and data analysts will remain blinded to group allocation throughout the data collection and statistical analysis phases.

The primary outcome is patient all-cause mortality rate: Assess whether the in-hospital mortality rate decreases after the intervention, reflecting the AI-assisted detection system’s ability to identify life-threatening conditions in a timely manner and facilitate rapid clinical intervention.

The secondary outcomes are as follows:

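### The stated 80% power is not delivered: 18 units at ICC 0.01 with 5450 patients per group give about 36–38%, and more patients in 18 units cannot reach 80%

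*Protocol article*

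**What the plan says.** Protocol article, Determination of Sample Size: the primary outcome is in-hospital mortality, with a control rate of 28% taken from institutional data. On the alternative: "A projected reduction to 25% was used for the sample size calculation". The result is then stated: "With an intraclass correlation coefficient of 0.01, a power of 80%, and a 1-sided α of 5%, each group requires 5450 patients", for a total of 10,900. The paragraph concludes: "This design is expected to provide sufficient power to detect clinically significant improvements in patient outcomes". It gives no number of units, unit size or design effect.

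Protocol article, Research Design: "A total of 18 ICU units will participate, with NTUH contributing 14 units and the remaining hospitals contributing 2 units each". These units are what is randomized. The section on Phase 2 ranks units on a random number within strata of ventilator use and allocates them by odd or even rank, which gives about 9 units per group.

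**The concern.** In a cluster trial, power depends on the number of clusters as well as the number of patients. The sample size paragraph uses an ICC, so an allowance for clustering was evidently made, but the allowance in 5450 looks far too small for 18 large units.

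If so, readers, funders and ethics committees are told that the trial has a four-in-five chance of detecting a 3-point mortality reduction when the real chance is much lower. A null result after two years in three hospitals could then be read as evidence that the system does not affect mortality, when the trial was never able to show it.

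**Working it through.** **Inputs.** From Determination of Sample Size: p1 = 0.28, p2 = 0.25, ICC ρ = 0.01, one-sided α = 0.05, power 80%, n = 5450 per group. From Research Design: 18 units. Assumed: 9 units per group of equal size. The split is inferred from the odd/even allocation and is the most favourable split of 18.

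**1. Trying to reproduce 5450.** Without clustering:

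n = (1.645 + 0.842)² × (0.28×0.72 + 0.25×0.75) / 0.03² ≈ 2673 per group (2675 with pooled variance; 2742 with continuity correction).

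5450 / 2673 = 2.04. With design effect DE = 1 + (m − 1)ρ, a DE of 2.04 means m = 1 + 1.04/0.01 ≈ 105 patients per unit, and 5450/105 ≈ 52 units per group. With continuity correction, m = 100 gives 2742 × 1.99 = 5457, close to the stated figure, but that implies 54–55 units per group. Two-sided versions imply an even smaller m (about 58–62). No variant gives 5450 with 9 units per group.

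**2. Power of the design as described.**

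- m = 5450/9 = 605.6
- DE = 1 + 604.6 × 0.01 = 7.05
- Effective n = 5450/7.05 ≈ 774 per group
- SE of the difference = √[(0.2016 + 0.1875)/773.5] = 0.02243
- 0.03/0.02243 = 1.338
- Power (normal) = Φ(1.338 − 1.645) = 37.9%
- Power (noncentral t, 16 df) = 35.8%
- Beta-binomial simulation, 9 v 9 units of 606, unit-level t test, 40,000 runs: 35.8%

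At two-sided 5%, power is 26.7% (normal) or 24.1% (t).

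**3. The ceiling.** As m grows, effective n tends to 9/0.01 = 900 per group, below the 2673 required. Power then tends to 42.0% (normal) or 39.6% (t).

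**4. Units needed at ICC 0.01.** The lower bound is 2673 × 0.01 = 26.7, so at least 27 per group (28 by t), and only with practically unlimited patients per unit. At the planned 5450 per group, about 52–53 units per group are needed (normal; 54 by t).

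**5. Dependence on the ICC.** For 9 v 9 units and 5450 per group, one-sided 5%, normal / t:

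| ICC | Power for 28% v 25% | Reduction from 28% detectable with 80% power (points) |
|---|---|---|
| 0.001 | 88% / 85% | 2.7 / 2.8 |
| 0.002 | 77% / 74% | 3.1 / 3.3 |
| 0.005 | 55% / 52% | 4.2 / 4.4 |
| 0.01 (stated) | 38% / 36% | 5.5 / 5.7 |
| 0.02 | 25% / 24% | 7.4 / 7.7 |

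Power reaches 80% only if the ICC is about 0.0017 (normal) or 0.0014 (t).

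**6. Unequal unit sizes.** With DE = 1 + [(1 + CV²)m − 1]ρ and assumed CVs of 0.3 to 0.65, normal-approximation power falls to 36–31%.

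**The case against.** The best case for the plan has four parts.

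- **The ICC is uncertain.** It is given without a source, and at 0.001 the design would have more than 80% power. The ceiling on power is therefore conditional on an ICC near 0.01. That is true, but 0.01 is the plan's own figure, and the 80% is claimed at that value.
- **Stratification by ventilator use may reduce between-unit variance.** It may, if the analysis uses it. The residual ICC would have to fall from 0.01 to about 0.0014–0.0017, and the plan claims no such gain.
- **The planned test is a simple comparison of proportions, and an article may leave the cluster adjustment to the analysis plan.** The 36–38% does assume an analysis that respects clustering. Without adjustment, simulation gives about 76% rejection at 28% v 25%, still below 80%, with a one-sided type I error of about 27% instead of 5%. Those extra rejections are false-positive risk, not power.
- **The primary outcome may change after the pilot.** The text after Figure 3 says so. This does not correct the figure given for mortality. It does mean that the calculation must be repeated for whatever primary outcome is finally fixed.

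The finding also does not rest on something an article may omit: the ICC, patient number, power and number of units are all stated, and they conflict. What stands from the other side is that the assumed unit size of about 100–105 is an inference about how 5450 arose, not something the plan states.

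**Conclusion.** The concern holds. At the plan's own ICC of 0.01, with 18 units and 5450 patients per group, power for 28% v 25% at one-sided 5% is about 36–38%, less than half the stated 80%. A true 3-point benefit would be missed nearly two times in three. The number of units is the binding constraint, so a larger recruitment target does not help.

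This rests on 9 equal-sized units per group and a cluster-respecting analysis. An uneven split or unequal unit sizes lower power further. Only an ICC about six to seven times smaller than the one stated would rescue the claim.

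**What to change.** Rewrite the sample size paragraph for the actual number of units:

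1. State the number of units per group, the mean unit size (about 606) and the design effect (7.05 at ICC 0.01).
2. Give power for 28% v 25% as about 36% (one-sided 5%, ICC 0.01, 9 units per group, t with 16 df), and the difference detectable with 80% power as about 5.7 points (28% to about 22.3%).
3. Show both over ICC 0.001 to 0.02, as in the table above, and give the source of the ICC.
4. Delete the sentence claiming adequate power. State that a non-significant mortality result is inconclusive and will be read from its confidence interval.
5. Show the two-sided 5% power (about 24% by t, 27% normal) alongside, because the Limitations section lists ways in which the system could do harm.
6. Repeat the calculation if the primary outcome is changed after the pilot.

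If 80% power for a 3-point reduction is to be kept, it has to come from more units: about 52–54 per group at 5450 patients per group and ICC 0.01.

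The cost of items 1–6 is a rewritten paragraph, a matching correction wherever the power claim is repeated, and a much less favourable power statement. No extra patients and no change to care are needed.

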### Statistical and Cost-Effectiveness Analysis

Statistical analysis will be conducted using SAS software (SAS Institute) to evaluate the outcomes of this study. Continuous variables, such as clinical outcomes and procedural times, will be summarized using descriptive statistics, including the number of observations, mean, median, SD, range, and 95% CIs. For categorical variables, frequency counts and percentages will be used to summarize the data.

In terms of clinical effectiveness, the primary outcome will be in-hospital mortality, and a proportional test will be used to compare the mortality rates between ICUs that have implemented the AI-assisted detection system and those that have not. The secondary clinical outcomes, which include the length of stay in the hospital, time to detect tube misplacements, and the time taken for medical interventions (such as repositioning of ETT and NGT and placement of pneumothorax drainage), will be analyzed using *t* tests for continuous variables. For categorical outcomes, including the rates of misplacement and other related interventions, chi-square test will be used. In addition, proportional tests will be conducted to examine the differences in the frequency of interventions across the 2 groups.

The study will also incorporate a health care technology and economic evaluation framework to assess the cost-effectiveness of the AI system alongside its clinical effectiveness. This evaluation will explore whether the clinical benefits derived from the AI system justify the associated resource consumption. Previous research by the team [21], such as the use of Markov models in gastric cancer screening and prevention, has demonstrated the utility of such economic evaluations, particularly in quantifying the cost-effectiveness of medical interventions and their impact on mortality reduction.

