### Limitations

Although this study is classified as low risk, the AI system used may present potential indirect risks. One concern is the possibility of false positives or negatives, where the system may inaccurately identify medical images, leading to missed diagnoses or misplacements, delaying treatment or causing unnecessary interventions.

Another risk is overreliance on the system by health care providers, particularly if they are unfamiliar with its use, which could affect decision-making accuracy. In addition, system errors or delays may occur, increasing clinicians’ workload if the AI system fails to provide timely assistance. In addition, as the system analyzes patients’ CXR images, there is a risk to patient privacy if proper data protection measures are not in place, potentially compromising confidentiality.

To address potential risks, a pilot study will validate the AI system’s sensitivity and specificity, ensuring reliability. The AI system serves only as a supplementary diagnostic tool, with final decisions made by physicians based on its outputs and clinical information. Health care providers will receive training on the system’s operation, limitations, and result interpretation to prevent overreliance. Regular feedback meetings will address issues as they arise. A monitoring protocol will log processing times and detect errors. In case of delays or malfunctions, standard diagnostic protocols will be followed. The AI software will also be approved by the NTUH Smart Medical Center to ensure data security and system integrity.

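### The primary mortality comparison is sized at an unjustified one-sided 5% level although the protocol itself describes how the CAD system could cause harm

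*Protocol article*

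**What the plan says.** All the design figures are in Determination of Sample Size. The control rate is given as "the ICU mortality rate in 2023 to 2024 is estimated at 28"%, and "A projected reduction to 25% was used for the sample size calculation". The paragraph continues "With an intraclass correlation coefficient of 0.01", 80% power and "a 1-sided α of 5"%, and concludes that "each group requires 5450 patients, resulting in a total sample size of 10,900". It does not state a cluster size or a reason for the one-sided level.

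Research Design words the primary outcome as a question about a decrease in mortality, and says "A total of 18 ICU units will participate, with NTUH contributing 14 units" and the other two hospitals contributing two each. Statistical and Cost-Effectiveness Analysis names a proportional test for mortality without saying whether it is one- or two-sided.

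On harm, Limitations says that the system may misread images, "leading to missed diagnoses or misplacements, delaying treatment or causing unnecessary interventions", and adds overreliance and system delay as further risks. Ethical Considerations says that delays or technical faults could postpone treatment in critical care.

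**The concern.** A one-sided test is easiest to defend when an effect in the other direction is implausible or would not matter. Here the endpoint is death, and the protocol names several routes by which the device could worsen care. Patients also do not consent individually, on the argument that participation adds no risk.

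Two things follow from the stated level. A claim of reduced mortality would need only z > 1.645, not z > 1.96. And no result in the harmful direction, however large, falls in the rejection region of the test the trial was sized for. The power figure also depends on this choice, so a reader who assumes the usual two-sided 5% test will take 80% to mean more than it does.

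**Working it through.** **Inputs.** From Determination of Sample Size: p1 = 0.28, p2 = 0.25, difference 0.03, ICC 0.01, power 80%, one-sided α 0.05, 5450 per arm. From Research Design: 18 units. Assumed: 9 units per arm of equal size.

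**1. Patients per arm before clustering.** n = (z_α + z_β)² × [p1(1−p1) + p2(1−p2)] / 0.03², with 0.28×0.72 + 0.25×0.75 = 0.3891.
- One-sided 5%: (1.645 + 0.842)² × 0.3891 / 0.0009 ≈ 2,673
- Two-sided 5%: (1.960 + 0.842)² × 0.3891 / 0.0009 ≈ 3,393, which is 27% more

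A pooled-variance formula gives 2,675 and 3,397.

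**2. The protocol's 5450.** It cannot be reproduced from the stated inputs alone, because no cluster size is given. The implied design effect is 5450 / 2,673 = 2.04. Solving 1 + (m − 1) × 0.01 = 2.04 gives m ≈ 105 patients per unit, or about 52 units per arm. With a continuity correction, 2,742 × 1.99 = 5,457 at m = 100. So 5450 fits a one-sided 5% calculation with an assumed cluster size of about 100 to 105.

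**3. Error rate.** P(z > 1.645) = 5.0% and P(z > 1.960) = 2.5% under no effect. The nominal false-positive rate for benefit is therefore twice that of a two-sided 5% test.

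**4. Sidedness alone, at design effect 2.04.** SE = √(0.3891 / 2,673) = 0.01207, and 0.03 / 0.01207 = 2.486.
- One-sided 5%: Φ(2.486 − 1.645) = 80%
- Two-sided 5%: Φ(2.486 − 1.960) = 70%

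On the same assumption, 80% power two-sided would take 3,393 × 2.04 ≈ 6,920 per arm.

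**5. With the 18 units.** m = 5450 / 9 ≈ 606; design effect = 1 + 604.6 × 0.01 ≈ 7.05; effective n = 5450 / 7.05 ≈ 774 per arm; SE = √(0.3891 / 774) = 0.0224; 0.03 / 0.0224 ≈ 1.338.
- One-sided 5%: Φ(1.338 − 1.645) ≈ 38%
- Two-sided 5%: Φ(1.338 − 1.960) ≈ 27%

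Using t on 16 degrees of freedom, these become about 36% and 24%.

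**6. Can enrolment make up the loss?** With 9 units per arm and ICC 0.01, the effective n per arm cannot exceed 9 / 0.01 = 900 however many patients are enrolled. That is below both 2,673 and 3,393.

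**The case against.** The protocol discloses its level and is consistent about direction: it asks only whether mortality falls. It calls the risks indirect and lists controls, including pilot validation, physicians keeping the final decision, training, error monitoring and fallback to standard procedures. The level appears only in the sample-size paragraph, and the sidedness of the reported test could be set in an analysis plan that is not shown. The primary outcome may also change after the pilot. All of this is fair, and it limits the point to an unexplained design choice. It does not remove it: mortality is the stated primary outcome, one-sided 5% is its only stated level, and controls that reduce a risk do not make harm implausible. If a two-sided test is intended, the 80% does not belong to it.

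Three stronger readings are tempting, and the document does not support them.
- A reader might see a conflict with the 95% CIs in the analysis section. Those belong to descriptive summaries of continuous variables, "including the number of observations, mean, median, SD, range, and 95% CIs". Mortality is binary, and no interval for its difference is specified there.
- A reader might say that one-sidedness inflates the stated power. At a design effect of about 2.04, 80% is the correct figure for the level disclosed; 70% is the power of a different test.
- A reader might say that harm could not be shown at all. A one-sided rule limits what may be claimed as benefit; it does not prevent an excess of deaths from being estimated and reported.

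The doubling is also nominal. The proportional test is described without a cluster adjustment. Run unadjusted at a design effect of 7.05, its false-positive rate for benefit would be about 27% at z > 1.645 and 23% at z > 1.960. That is a separate and larger problem, which a change of sidedness would not cure.

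**Conclusion.** The point stands in a limited form. The only stated level for the primary comparison is one-sided 5%, without justification, in a protocol that itself describes plausible routes to harm. The firm consequences are a nominal 5% rather than 2.5% false-positive rate for benefit, and a rejection region with no harmful outcomes in it.

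The power figures are conditional. The fall from 80% to 70% rests on a design effect inferred from the stated total, not one the protocol gives. The 38% and 27% rest on 9 equal units per arm and the protocol's own ICC of 0.01. Clustering alone takes 80% to 38%; sidedness accounts for the further step to 27%. Sidedness is therefore not the main reason the 80% cannot be relied on, but any restatement of power has to take account of both.

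**What to change.** State the primary mortality test as two-sided 5%, or equivalently for benefit as one-sided 2.5%. In either case, specify that the mortality difference will be reported with a two-sided 95% CI, so that an excess of deaths is as visible as a reduction. Put the sidedness in the analysis section as well as the sample-size paragraph.

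Keep enrolment at 5450 per arm and restate its power on the new basis with the actual 18 units: about 27% two-sided under the protocol's rates and ICC, with the cluster size and design effect shown. Do not restate it as 70%, because that figure assumes units of about 105 patients, which 18 units and 10,900 patients do not give.

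The cost is wording and a much less favourable power statement. No additional patients or data are needed, and the randomised phase is dated from January 2026, after the article's publication in August 2025.

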**Figure 3 figure3:**
[figure not shown]
Illustration of study design. AI: artificial intelligence; FJCUH: Fu Jen Catholic University Hospital; ICU: intensive care unit; NTUH: National Taiwan University Hospital.

Because the causes of death in patients admitted in ICU may not necessarily be related to CXRs, adjustments to the primary outcome of the formal trial will be made following the pilot testing. This will involve evaluating and modifying the primary outcome (eg, time to detection of misplacement) to better align with the trial’s objectives and needs.

The conduct and reporting of the trial follow the CONSORT (Consolidated Standards of Reporting Trials) 2010 statement with the extension to cluster randomized trials [20].

### Recruitment and Enrollment

#### Phase 1: Pilot Study

During this phase, the emergency critical care (ECC) area and ICUs at NTUH will be selected as the pilot sites for system testing and preliminary evaluation. The implementation period will last approximately 6 months to 1 year from January 1 to December 31, 2025. Attending physicians, resident physicians, and advanced practice nurses from the ECC and ICUs will sign consent forms, enabling them to use the CAD system upon agreement.

Simultaneously, an exemption from patient informed consent will be requested, as the study is classified as minimal risk. The potential risks to study participants do not exceed those encountered by nonparticipants, and the exemption will not adversely affect their rights or welfare.

The inclusion and exclusion criteria are shown in Textbox 1.

The inclusion and exclusion criteria for the pilot study.
**Units**
Inclusion criteriaEmergency critical care or intensive care units at National Taiwan University HospitalThe units included the patients requiring chest x-rays due to endotracheal intubation, nasogastric tube insertion, or ventilator use with a risk of pneumothorax.Exclusion criteriaThe unit supervisor does not agree to participate in the trial.The unit is unable to implement the artificial intelligence–assisted system (eg, no data connection or system support).
**Patients**
Inclusion criteriaPatients who are adults and require chest x-ray due to one of the following conditions: endotracheal intubation, nasogastric intubation, or the use of a ventilator with the potential to cause pneumothorax.Exclusion criteria for patients in isolation wards or pediatric wardsPatients in isolation wardsPatients in infant intensive care unit

The data collected includes the total number of patients in the ward, ventilator use, pneumothorax cases, CXR results, misplacement detection time, mortality rate, length of stay, ETT and NGT resetting times, pneumothorax drainage tube placement time, direct medical costs (eg, x-ray examinations, intubation fees, and hospitalization fees), and indirect costs (eg, CAD system and labor costs). System error messages will be recorded. Imaging data will not be collected, and the AI software will not undergo model training. A midterm evaluation at the end of phase 1 will determine the feasibility of phase 2.

